**STUDY ACTIVATED**

August, 1993

**Addendum #1**, 11/93: Changed SWOG SC (Cover, Index); Removed ref to tent act date of lab prot E3293 (Schema, Sec. 3.0, Sec. 4.0, Sec. 10.0).

**Addendum #2**, 6/94: Gender and Race/Ethnic issues; HHS 596 & ADR forms updated; NCI ADR FAX # added; baseline CXR time frame clarified; typos corrected: (Secs. 1.0, 4.0, 5.3, 11.0, 13.0).

**Addendum #3**, 3/95: NSABP added as participant (Title, Index, Secs. 3.0,4.0, 4.5, 4.6, 5.32, 11.2), changed Statistician (Title), changed [name]., address (Index), added elig crit for CEA testing time of  $\leq$  2 weeks before reg (Sec. 3.104, 3.304), updated contraception crit (Secs. 3.113, 3.316), updated reg procedures, updated ECOG address (Sec. 4.0), updated DMO zip code (Sec. 5.32), dose mod clarification (Sec. 5.422), added clarifying footnotes to CEA, Colonoscopy, and Preg tests (Sec. 7.0, table), trademark added to Ergamisol (Levamisole, other names) (Sec. 8.2), updated Levamisole incompatibilities (Sec. 8.26), updated Levamisole neurological tox (Sec. 8.28 and App. I), updated path sub (Sec. 10.0, App. III), updated PCO address (Sec. 10.41), changed tense from first person to second, updated Levamisole side effects (App. I), updated CTC table (App. II), updated PCO address and tel number (App. III).

**Addendum #4**, 9/95: SWOG phone # added (Index page), Corrected typos (Sec. 1.1, 4.2, 9.0, Schema), Clarified numbering (Sec. 3.0), Updated ECC Name + Address (Secs. 4.0, 5.0, 10.4, 10.42, 11.0, App III), clarified Dose Mods (Sec. 5.421).

**Addendum #5**, 7/96 - CALGB added to ancillary lab study E3293 (Secs. 3.0, 4.0, 7.2, 10.0, 10.2, 10.22, 10.23, 10.41, 10.42, App III), ECOG Path Chair updated (Title, App III), PIN contact updated (Index), checklist added to Sec. 11.0.

E1292  
SWOG 9250  
CALGB 9395  
NSABP C163  
ACOSOG E1292  
EPP E1292  
INT 0136

**Addendum #6, 9/97** - Changed adj chemo from 12 months of 5-FU/Levamisole to 6 months of 5-FU/Leucovorin; Frozen tissue samples no longer being collected; ECOG PCO address/phone/fax updated; Updated Sec. 5.33; ECOG Fax # added to ADR Sec.; Added and renumbered references; Enrollment in E1295 mentioned as possibility for patients with diarrhea/tox; Reregistration directions in schema corrected; Study parameters for Dukes' B3 and C patients moved to below table; Timepoints for flow sheets sub clarified; NSABP SC name and address updated; INT-0089 study number and accrual added; Preop and Postop Eligibility Criteria consolidated; Schema perioperative chemo directions clarified; Objective pertaining to effect of perioperative continuous 5-FU on survival of Dukes' B2 patients elucidated; Statement that Dukes' B2 patients are followed on observation until relapse/death deleted; Reference made to ADR table; References renumbered; Secs. renumbered; Typo corrected; Dukes' stage specified under follow-up time points in Sec 7.0. **REVISED PROTOCOL.**

**Addendum #7, 4/98** - Removed thrombocytopenia from listing of potential side effects of Leucovorin (Section 8.210); Typo corrected (Section 9.0); Reformatted Informed Consent to reflect current template (Appendix I); Moved info about tissue testing to new template (Appendix I).

**Addendum #8, 8/99** - Schema reformatted (Schema); Added ACOSOG (Cover, Index, Secs. 3.0, 4.0, 4.6, 4.7, 5.35, 5.36, 10.0, 11.3); Added EPP (Cover, Index, Secs. 3.0, 4.0, 10.0, App. VI); NSABP Study Coordinator changed (Cover, Index); ECOG Statistician changed (Cover); Address for ECOG and CALGB Study Chair and SWOG Study Coordinator changed (Index); PIN Contact Person changed (Index); AGC  $\geq 1500/\text{mm}^3$  changed to WBC  $\geq 3000/\text{mm}^3$  (Secs. 3.14, 3.28); CEA levels changed from required to optional (Secs. 3.1142, 3.1152, 7.1 footnote 2); ECOG zip code changed (Secs. 4.0, 5.32, 11.0); Changes to NSABP Registration/Randomization instructions (Sec. 4.5); Changed Grades 1-5 to Grades 4-5 (Sec. 5.32 table); AGC changed to WBC (Secs. 5.41, 7.1, 7.2); "Granulocytopenia ( $< 1500/\text{mm}^3$ )" changed to "Leukocytopenia ( $< 3000/\text{mm}^3$ )" (Sec. 5.41); Deleted "SWOG" (Sec. 5.52); Changed "below" to "above" (Sec. 7.2); Deleted reference to red blood cells (App. I, Risks and Discomforts); Deleted "SWOG" and "NSABP" (App. III Memorandum).

**Addendum #9, 12/08**

**Update #1, 3/10**

E1292  
SWOG 9250  
CALGB 9395  
NSABP CI63  
ACOSOG E1292  
EPP E1292  
INT 0136  
**REVISED**

Revised 8/99, Addendum #8

# SCHEMA

[figure not shown]

## **RANDOMIZATION:**

Patients will be randomized pre-operatively within 2 weeks of surgery, or post-operatively within 24 hours of surgery, for primary colon cancer with no known metastases. If metastatic disease is found during surgery, or if there is unresectable residual disease after surgery, the patient will be taken off-study, if already randomized, and followed for survival.

## **PATHOLOGIC STAGING: (within 2 weeks after surgery)**

All patients staged with Dukes' A, B1, and D disease will be taken off study and followed for survival. Those patients staged with Dukes' A, B1, and D disease who were randomized to receive perioperative 5-FU will have this perioperative 5-FU discontinued. Patients staged with Dukes' B2, B3, or C disease must be re-registered (see below).

## **RE-REGISTRATION: (Within 35 days after surgery)**

Dukes' B2 patients must be re-registered to observation. Dukes' B3 and C patients must be re-registered to adjuvant chemotherapy with 5-FU plus leucovorin. Dukes' A, B1 and D patients will not be re-registered.

## **SUBMISSION OF PATHOLOGY MATERIALS: SLIDES/PARAFFIN BLOCKS = within 1 month after surgery)**

The submission of paraffin blocks and H&E slides of tumor and normal colonic mucosa is required for ECOG patients entered on this study. See Section 7.2 and 10.0 for details.

**NOTE:** When randomizing ECOG and CALGB patients to E1292/C9395, it is strongly encouraged that they be simultaneously registered to laboratory companion protocol E3293

## 1.0 INTRODUCTION

Over 110,000 new cases of colon carcinoma are diagnosed every year in the United States. Over 50,000 of these patients will die of this disease. Thus, approximately 45% of patients who get colon carcinoma will die of distant metastases or, more rarely, local recurrence (1). The purpose of this study is to look at the effects of intravenous perioperative 5-FU therapy, followed by adjuvant 5-FU/leucovorin, on the disease-free interval and survival for colon cancer. Studies that support this therapy are cited below, and involve either intravenous or portal vein perioperative 5-FU therapy.

This study and the NSABP study came to the same conclusion: the regional approach of adjuvant chemotherapy through the portal vein does not lower the incidence of liver metastases but the perioperative portal infusion of 5-FU does increase survival in Dukes' C patients (5). Both the NSABP study and the English study found that the perioperative chemotherapy seemed to have an effect after 3 years of follow-up. The majority of adjuvant trials in which chemotherapy was given post-operatively at least a week later show more immediate outcome improvement. This temporal difference in outcome improvement may be explained by postulating different mechanisms of action of these 2 adjuvant approaches. If that is correct, a combination of the two approaches may be beneficial.

There are several trials in progress assessing the efficacy of different regimens of intravenous adjuvant chemotherapy, all including 5-FU and some modulator. In October 1989, the North Central Cancer Treatment Group (NCCTG) and the Mayo Clinic published a report indicating a disease-free survival benefit for levamisole plus 5-FU (p = .02) when given as adjuvant therapy for colon cancer. This difference was observed predominantly in the Dukes' C patients. There was also a survival benefit but only in the Dukes' C patients (6).

An intergroup study was then performed and reported in 1990 (7) and updated in 1992 (8). This study randomized over 1200 patients with Dukes' B2 or C colon cancer to receive post-operative adjuvant therapy with levamisole alone, levamisole plus 5-FU or observation. The follow-up time was 5 years. There were 168 recurrences in the observation arm, 162 with levamisole alone, and 112 with levamisole + 5-FU. Deaths were 153, 144, and 108 respectively. Levamisole plus 5-FU decreased cancer related deaths by 32% ( $p < 0.004$ ). The toxicity was low for this regimen; therefore, the authors recommended that 5-FU plus levamisole should be the standard for adjuvant chemotherapy in patients with Dukes' C colon cancer.

The mechanism of action for levamisole is not clearly understood. Levamisole alone did not have an effect on survival in the adjuvant setting. No single immunomodulatory effect of levamisole can be specified that would account for its beneficial results when combined with 5-FU. Levamisole has been studied extensively "in vitro." It has been shown to increase chemotaxis of monocytes and to restore defective neutrophils among other activities. Levamisole seems to be more effective "in vivo" than can be proved by the "in vitro" studies. This may be because levamisole is acting indirectly, such as increasing the production of a lymphokine which would be tumorocidal. Also, levamisole may restore immune functions in patients with cancer or post surgery that cannot be detected in the laboratory situation. The exact mechanisms of action have yet to be elucidated (9).

In 1982, a randomized study was begun in Australia and New Zealand. Patients with colon cancer were randomized pre-operatively into one of 3 treatment arms:

1. 5-FU 600 mg/m^2/d for 7 days immediately following surgery given via a catheter into the portal circulation.
2. 5-FU 600 mg/m^2/d for 7 days immediately following surgery given into the systemic venous circulation.
3. No post-operative chemotherapy.

A total of 372 patients were randomized as of 1987. Of these, 232 were analyzable and 140 were ineligible (25 no cancer, 40 Dukes' A, 75 Dukes' D, 35 no follow-up).

The post-operative chemotherapy was well tolerated. The study at this time suggests that patients with portal vein chemotherapy have improved survival, but follow-up is not long enough to make any conclusions since the study was ongoing at the time of the report. However, this study has provided evidence that immediate post-operative 5-FU can be given safely with a schedule of 600 mg/m^2/d for 7 days (10,11).

In 1992, the large intergroup study of adjuvant chemotherapy for colon cancer, INT-0089, was closed after accruing 3,794 patients. This study compared the standard chemotherapy regimen of 5-FU + Levamisole for 12 months to 3 other treatments:

1. Low dose Leucovorin + 5-FU
2. High dose Leucovorin + 5-FU
3. Low dose Leucovorin + 5-FU + Levamisole

All 3 regimens are given for 6 months.

In 1996, an interim analysis demonstrated no significant differences in the disease-free survival or overall survival for any of the arms. This was reported at the ASCO meeting in May, 1996 (12). Because there were no differences in outcome and because the duration

Rev. 9/97 of the treatment for all the leucovorin arms was 6 months vs. the 12 months length of the 5-FU/Levamisole arm, the 5-FU/low dose leucovorin arm has emerged as the obvious choice for treating patients in the community. Further close analysis and follow-up of greater than 4 years has held up these findings (13).

Rev. 9/97 The study proposed in this concept combines the perioperative approach with the now standard adjuvant chemotherapy for colon cancer, 5-FU and leucovorin. Since all the previous studies mentioned have shown a benefit for Dukes' C patients, all Dukes' C patients will receive the 5-FU/leucovorin. The proper treatment for Dukes' B patients is not as clear since many studies did not show a statistically significant benefit for this group. Because of these data, the Dukes' B2 patients will be randomized for the perioperative part of this study only. They will not receive the post-operative 5-FU/leucovorin.

Rev. 9/97 For the B3 patients, although no study has proven a benefit for adjuvant chemotherapy, it is also true that the studies have not been large enough to look specifically at the subgroup.

Because of the poorer survival of this group it is felt they should be treated in the same fashion as the C patients and be eligible for both stages of the protocol.

## 1.2 Prognostic Markers (see laboratory companion protocol, E3293, for details)

The chromosomal and molecular genetic alterations in colorectal cancer are beginning to be defined. It seems clear that a number of oncogenes (which are tumor promoting genes) and tumor suppressor genes (which restrain tumor growth) contribute to the development of colorectal cancer (9).

Rev. 6/94 Allelic losses have been observed on almost all chromosomal arms in colorectal cancer with some of the alterations seen more consistently than others. The most common sites for these losses are on chromosomes 1, 5, 8, 17, and 18. Tumor suppressor genes have been localized to some of these chromosomes, such as the APC (Adenomatous Polyposis Coli) gene and MCC (mutated in colorectal cancer) gene on 5q, the p53 gene on 17p and DCC (deleted in colorectal cancer) gene on 18q.

Rev. 6/94, 9/97 Understanding of the clinical utility of the identified genetic alterations is in its infancy. Initial data from three series of patients suggest that allelic deletions involving the p53 gene on chromosome 17p (14) and the DCC gene on chromosome 18q (15) may be of prognostic value. There is, however, conflicting evidence from these studies as to the prognostic value of the deletions. Only 17p allelic deletion was found to be associated with poor prognosis in one study, while only 18q deletion was associated with poor survival in another study (14, 15). A large prospective study is needed to answer the question of validity of these markers for general clinical usage. Furthermore, no study has addressed the issue of chemotherapy response in relation to molecular genetic alterations. Laboratory companion protocol, E3293, will provide us with over 1000 tumor specimens to define the role of p53 and DCC in the prognosis of colon cancer.

Rev. 6/94, 9/97 Furthermore, it is not known if patients who benefit from chemotherapy have a different chromosomal pattern than those who do not respond. This laboratory study will also provide a prospective trial of the chromosomal patterns present in patients and could be compared with the effectiveness of chemotherapy in those patients.

Rev. 6/94

### 1.3 Gender and Racial/Ethnic Issues in E1292

#### 1.31 Evidence For/Against Treatment by Gender Interactions in the Effects of Perioperative 5-Flourouracil

Rev. 9/97

Rev. 9/97  
 Rev. 9/97

Rev. 9/97

Rev. 9/97

To our knowledge there is no literature addressing this issue for perioperative treatment. More generally, there has been little attention paid to gender differences with respect to treatment, and no ECOG colon study has shown any gender related interactions with adjuvant therapy. A review of recent papers reporting the effects of postoperative 5-FU in colorectal cancer shows three studies suggesting possible gender interactions with treatment, but they are in conflict with regard to the direction of effect. A 1988 NSABP rectal study (16) showed increased disease-free survival of MOF over no adjuvant treatment in males but the corresponding 1988 colon protocol (17), using the same MOF schedule, showed no gender interaction. A 1989 NCCTG colorectal study (18) reported an increase in disease-free survival in females for their 5-FU plus levamisole arm in a subset analysis. In contrast, a second NCCTG study in colon cancer conducted in 1990 (7) showed, in subset analysis, a differential benefit in males due to 5-FU plus levamisole. In addition, a recent paper on 5-FU clearance in head and neck cancer (19) demonstrated lower clearances in females but the doses examined in that study were higher than those used in this colon study (500 used in this colon study (500 to 1,000 mg/m^2). Other recent colorectal studies involving 5-FU (20-23) reported no gender by treatment interactions. It is important to interpret the conflicting results of the subset analyses cautiously, since exploratory data investigations can often lead to spurious associations that would not be reproducible.

Thus at present there appears to be no strong evidence for a gender by treatment effect involving 5-FU used as a postoperative adjuvant in colon cancer, and no indication that treatment differences may exist in the perioperative setting.

#### 1.32 Evidence For/Against Treatment by Racial/Ethnic Interactions in the Effects of Perioperative 5-Flourouracil

We are aware of essentially no literature addressing this issue for 5-FU therapy or for any other adjuvant therapy in colorectal cancer, as the issue of different effects within racial/ethnic groups has received little attention in this disease. Thus at present there is no evidence either for or against the possibility of racial/ethnic group by treatment effect interactions for this study.

#### 1.33 Gender and Racial/Ethnic Representation

Based on accrual to the recent intergroup colon adjuvant trial, E2288, we expect roughly 55% of the cases on E1292 to be male and 45% to be female; 86% of cases to be white, 2.1% to be hispanic, 10% to be black (non-hispanic), 1.2% to be Asian/Pacific Islander, and <0.5% to be native American. The proportion of minorities could be somewhat higher, because of general efforts in ECOG to improve minority accrual on clinical trials. These efforts include conducting focus groups/workshops with community physicians who are not currently affiliated with a clinical cooperative group (especially physicians who treat a large number of minority cancer patients), and developing and implementing a marketing and outreach intervention to increase minority accrual.

#### 1.34 Design Considerations/Analysis Plans

In general there are no strong reasons to expect differential effects of 5-FU therapy in gender and minority subgroups, especially in the perioperative colon setting. The fact that studies reporting on gender effects are in conflict as to the direction of any treatment benefit leads to the possible conclusion that subset analyses may not be reproducible and therefore it may not be prudent to modify accrual objectives for this perioperative study based on them. Furthermore, there is no information to date on racial/ethnic differences in response to adjuvant treatment for colon cancer in general. Thus the study will also not have separate accrual targets for these subgroups.

Treatment assignment in the study will not be stratified on gender or racial/ethnic status since the randomization should automatically lead to reasonable balance in treatment assignments within gender and racial/ethnic subgroups. In the final analysis, the effect of therapy will be examined separately with these subgroups by plotting estimated disease-free survival and overall survival curves by treatment separately by gender and racial/ethnic subgroups. Tests for the effect of perioperative therapy within these groups will be conducted using log rank tests and by modeling treatment effects by gender and racial/ethnic group interactions in proportional hazards models.

### 2.0 **OBJECTIVES**

Rev. 9/97 2.1 To determine if adjuvant therapy with one week of continuous 5-FU given within 24 hours of a curative colon resection followed by 6 months of 5-FU/leucovorin is effective in prolonging the disease free interval and increasing survival in patients with Dukes' B3 or C colon cancer, when compared to patients who are treated with 5-FU/leucovorin only. Endpoints include: treatment failure--as defined by recurrence of local/regional or distant metastases--and survival.

Rev. 9/97 2.2 To determine if a week of perioperative continuous 5-FU affects disease-free survival and survival in patients with Dukes' B2 colon cancer.

2.3 To establish within ECOG a Central Tissue Repository for paraffin blocks and a frozen tissue bank.

**The following objectives apply to companion laboratory protocol, E3293:**

2.4 To confirm studies performed in smaller groups of patients to show that 17p deletion and 18q deletion are prognostic markers in a randomized setting.

2.5 To compare the response to chemotherapy in the different subgroups according to their chromosomal deletion profile.

### 3.0 **SELECTION OF PATIENTS**

Randomization will occur  $\leq$  2 weeks before the operation or within 24 hours after the operation, after consent is obtained. **No exceptions will be allowed.** Patients found to have residual disease or intraoperative metastatic disease outside of the draining lymph nodes will not receive the randomized treatment and will be treated off-study at the discretion of the participating investigator.

**If the patient is randomized PRE-OPERATIVELY, see Sections 3.1 and 3.2 for eligibility criteria. If the patient is randomized POST-OPERATIVELY, see Sections 3.1 and 3.3 for eligibility criteria.**

Rev. 11/93, 3/95,  
 7/96, 8/99

**NOTE: The submission of pathology material is required for ECOG patients and strongly encouraged for CALGB patients entered on this protocol (see Sections 7.2 and 10.0). Submission of tissue samples is not required for SWOG, ACOSOG, EPP or NSABP patients.**

**When randomizing ECOG or CALGB patients to E1292/C9395, it is strongly recommended that they be simultaneously registered to laboratory companion protocol E3293.**

Rev. 9/97

Rev. 9/95, 9/97

### 3.1 Eligibility Criteria

- 3.11 Must have adenocarcinoma of the colon documented by colonoscopy or barium enema.
- 3.12 Must not have a dual primary, as revealed by colonoscopy or barium enema.
- 3.13 Must start perioperative chemotherapy, if assigned, within 24 hours of the end of surgery.
- 3.14 Have WBC  $\geq 3000/\text{mm}^3$  and platelets  $\geq 100,000/\text{mm}^3$ ,  $\leq 2$  weeks prior to randomization.
- 3.15 Have adequate renal (serum creatinine  $\leq 2.0$  mg/dl) and hepatic function (bilirubin  $\leq 2.0$  mg/dl), within two weeks prior to randomization.
- 3.16 Have ECOG Performance Status of 0, 1 or 2 within 2 weeks prior to randomization.
- 3.17 No concurrent radiation or chemotherapy, prior exposure to 5-FU, or prior radiation or chemotherapy for this malignant disease.
- 3.18 No concurrent second malignant disease or any previous malignant tumor within the past 5 years except superficial squamous or basal cell carcinoma of the skin or *in situ* carcinoma of the cervix.
- 3.19 No history of non-malignant systemic disease that would preclude the chemotherapy treatment option.
- 3.110 Not pregnant or lactating.
- 3.111 Women of childbearing potential and sexually active males should use an accepted and effective method of contraception.
- 3.112 Must be  $\geq 18$  years of age.
- 3.113 Give written informed consent.
- 3.114 For Patients Randomized Pre-operatively
  - 3.1141 Must be randomized to the study no more than 2 weeks pre-operatively.

Rev. 3/95

Rev. 3/95, 8/99

- Rev. 9/95      3.115    For Patients Randomized Post-operatively
- 3.1151    Must be randomized to the study within 24 hours post-operatively so that the chemotherapy, if assigned, can begin no later than 24 hours after surgery.
- Rev. 3/95, 8/99
- Rev. 8/99      3.1152    Complete resection must have been performed with no evidence of residual disease or distant metastasis.
- Rev. 8/99      3.1153    Distal margin of the tumor must not extend below the peritoneal reflection in the area of the rectum.
- Rev. 8/99      3.1154    Single primary colon carcinoma without free perforation demonstrated. Patients with intestinal obstruction are eligible. Preliminary or complementary colostomy **does not** preclude entry of a patient.
- Rev. 9/95      3.2      Eligibility Criteria for Re-Registration (for patients randomized pre-operatively)
- All Dukes' B2, B3, and C patients must be re-registered  $\leq$  35 days post-op, after histopathological confirmation of tumor and Dukes' staging classification. Dukes' A, B1, and D patients will be removed from the study and will be treated at the discretion of their physician. Survival data will continue to be collected on Dukes' A, B1, and D patients until death.
- Rev. 9/97      Dukes' B2 patients will have perioperative 5-FU **continued** to completion, if so assigned, but will receive NO further adjuvant treatment.
- Rev. 9/97      Patients with Dukes' B3 and C disease must begin adjuvant 5-FU/leucovorin treatment between 21 and 35 days following surgery.
- 3.21      Must have pathologic classification of Dukes' B2, B3, or C disease (see Appendix IV for classification details) by the contributing institution.
- 3.22      Must be re-registered  $\leq$  35 days after surgery.
- 3.23      Have ECOG Performance Status of 0, 1 or 2.
- 3.24      Complete resection must have been performed with no evidence of residual disease or distant metastasis.
- 3.25      Distal margin of the tumor must not extend below the peritoneal reflection in the area of the rectum.
- 3.26      Single primary colon carcinoma without free perforation demonstrated. Patients with intestinal obstruction are eligible. Preliminary or complementary colostomy **does not** preclude entry of a patient.
- 3.27      Started perioperative 5-FU, if assigned, within 24 hours of surgery.

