#### 4.7 Cancellation Guidelines

Rev. 9/95

If a patient does not begin assigned treatment, the patient may be canceled. Reasons for cancellation should be submitted in writing to the following offices as soon as possible: For ECOG patients, to the ECOG Coordinating Center (ATTN: DATA); for CALGB patients, to the CALGB Central Office. Data will be collected on all canceled patients (see Section 11.0). **Note:** A patient may only be canceled if no protocol therapy is administered. Once a patient has been given protocol treatment, all forms should be submitted.

Rev. 3/95

For SWOG patients, the SWOG Statistical Center will not consider a patient canceled.

Rev. 8/99

For NSABP patients, the NSABP Biostatistical Center will not consider a patient canceled.

For ACOSOG patients, the ACOSOG Statistical Center will not consider a patient canceled.

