**9.0 STATISTICAL CONSIDERATIONS**

The primary objective of this study is to compare 6 months of adjuvant therapy with 5-FU and leucovorin to the same adjuvant therapy enhanced with perioperative therapy with continuous infusion 5-FU in Dukes' B3 and C patients with regard to the disease free interval and survival. This study is designed to be able to detect a clinically meaningful improvement in survival with 82% power while maintaining an overall significance level of 5% in a one-sided test, assuming patients are followed for 3 years after closure of the study to accrual. If 5 years of follow-up time were available, the power will be 91%. For Dukes' C patients, a clinically meaningful improvement in survival was taken to be an improvement in 5-year survival from 55% to 65%. For Dukes' B3 patients, this is an improvement in 5-year rates from 75% to 81%. To estimate the required sample sizes we assume exponential survival and a group sequential designed with an O'Brien-Fleming upper bound for early rejection of the null hypothesis of no treatment difference.

Assuming a 5-year survival rate of 75% for Dukes' B3 patients and 55% for Dukes' C patients in the adjuvant therapy alone arm, this study will require 800 analyzable patients (400 in each arm) to obtain the stated power using a stratified logrank test. Calculations assume that approximately 70% of the Dukes' B3 and C patients will be Dukes' C and 30% will be Dukes' B3. Since pathological staging is determined only after randomization, the accrual goal needs to be expressed in terms of Dukes' A,

B, C, and D patients. Using data on staging\* it is projected that 40% of all patients will be Dukes' B3 or C thus requiring a total accrual goal of 2000 patients to obtain the required number of B3 and C patients. As these projections are very approximate, accrual will be closely monitored during the first year and the accrual goals will be revised as necessary. For Dukes' A, B1, B2, and D patients, there will be no formal treatment comparisons. However, these patients will be followed to gather more information about disease progression and survival.

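### Starting perioperative 5-FU within 24 hours is written as an eligibility and re-registration condition that only the 5-FU arm can fail, and only after randomization; if it decides who is analyzed, the B3/C comparison can be biased

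*Protocol*

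**What the plan says.** - **Entry.** Protocol 3.13, in the eligibility list common to all patients: "Must start perioperative chemotherapy, if assigned, within 24 hours of the end of surgery". It cannot be known to be met when the patient is randomized.
- **Re-registration.** 3.27 (patients randomized before surgery) and 3.34 (patients randomized after surgery) both read: "Started perioperative 5-FU, if assigned, within 24 hours of surgery".
- **Enforcement.** 4.24 requires the re-registration criteria to be met and has the randomization specialist check them. It points to Section 3.2 or a Section 3.4 that does not exist; 3.3 is presumably meant. For B3 and C patients, re-registration is the step to protocol 5-FU/leucovorin.
- **Cancellation.** 4.7: "If a patient does not begin assigned treatment, the patient may be canceled", but only if no protocol therapy has been given. Not every group follows this: "For SWOG patients, the SWOG Statistical Center will not consider a patient canceled", and NSABP and ACOSOG say the same. Data are still collected on canceled patients (4.7, 11.0).
- **Analysis.** 9.0 states: "this study will require 800 analyzable patients (400 in each arm", with the aim of "maintaining an overall significance level of 5% in a one-sided test". It does not define analyzable. The only other use of the word is in 1.1, where a cited trial's 372 patients are split into 232 analyzable and 140 ineligible.

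**The concern.** Randomization makes the two B3/C groups comparable. Selecting on pathologic stage does little harm to that, because the stage of the resected tumor is not altered by an infusion begun after the operation. Selecting on whether assigned 5-FU was started is different. A control patient with the same early postoperative course has nothing to start, so stays in.

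The patients lost this way may have a worse prognosis. 5.41(c) stops the infusion for a significant postoperative complication, so the protocol itself expects some early complications to be incompatible with 5-FU. If such patients are removed from one arm only, an inert treatment looks beneficial and the 5% one-sided level is not kept.

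There is a second consequence even if nobody is deleted. A B3/C patient who did not start in time fails re-registration, while the matching control passes. The arms then have different access to the protocol's adjuvant therapy, which is supposed to be common to both.

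**Working it through.** **1. Reproduce the design.** Inputs from 9.0: 400 patients per arm, 70% C (280) and 30% B3 (120); 5-year survival 55% to 65% (C) and 75% to 81% (B3); exponential survival; final analysis at 6 years, read as 3 years of uniform accrual plus 3 of follow-up; one-sided 5%.

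- Hazard ratios: ln 0.65 / ln 0.55 = 0.721 (C); ln 0.81 / ln 0.75 = 0.732 (B3).
- Hazard λ = −ln(S)/5. Probability of death by the final analysis = 1 − (e^(−3λ) − e^(−6λ))/(3λ).
- Expected deaths: C 115.6 (control) + 89.5 (5-FU); B3 27.3 + 20.7; total 253.
- Stratified logrank drift, with variance (deaths)/4: Σ dₛ·|ln HRₛ|/4 ÷ √(253/4) = 2.582.
- Fixed-test power: Φ(2.582 − 1.645) = 82.6%. With the stated four-look boundary at 25/50/75/100% information: 81.5%.

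The protocol claims "a clinically meaningful improvement in survival with 82% power", so this reproduces. With 5 years of follow-up, about 336 deaths give 90.1% (90.9% fixed) against the stated 91%. The design figures are not in error on this point.

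**2. Apply the start rule to one arm, with no true effect.** The protocol gives neither the share f of patients who would not start in time nor their hazard m relative to the rest; both are assumed here. The 800 B3/C patients were simulated with a share f at hazard m in both arms. Non-starters were deleted from the 5-FU arm only, and the stratified logrank was applied (4,000 trials per setting). The sequential error is the chance of crossing the stated boundary given the simulated drift.

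| f | m | Apparent HR | Drift | One-sided error |
|---|---|---|---|---|
| 2–15% | 1 | 1.00 | about 0 | about 5% |
| 2% | 2 | 0.987 | 0.110 | 6.4% |
| 5% | 1.5 | 0.98 | 0.160 | 7.1% |
| 5% | 2 | 0.96 | 0.309 | 9.2% |
| 10% | 2 | 0.93 | 0.624 | 15.4% |
| 10% | 3 | 0.88 | 1.046 | 27.1% |

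Hand check: error ≈ 1 − Φ(1.645 − drift). For 5%/m=2, 1 − Φ(1.336) = 9.1%. For 10%/m=2, 1 − Φ(1.021) = 15.4%. Monte Carlo standard error near 9% is √(0.09×0.91/4000), about 0.5 points.

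**3. Keep everyone as randomized.** The simulated error is 4.5–5.1% in the same settings.

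**4. Let controls be lost too.** With f = 10% and m = 2, removing the matching controls as well returns the error to about 5%; removing half of them leaves 9.7%.

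**5. Power cost of keeping non-starters.** If they gain nothing, the drift becomes approximately 2.582(1 − f). To restore power takes 800/(1 − f)² B3/C patients, and total accrual is that divided by 0.40.

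| f | Drift | Power, 3 years | B3/C needed | Total accrual |
|---|---|---|---|---|
| 0 | 2.582 | 81.5% | 800 | 2000 |
| 2% | 2.530 | 80.1% | 833 | 2083 |
| 5% | 2.453 | 77.9% | 887 | 2217 |
| 10% | 2.324 | 74.0% | 988 | 2470 |

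**The case against.** **No passage removes these patients from the analysis.** This is right. A reader might infer that the protocol excludes non-starters and that the result is therefore biased. The text does not say so: 3.27 and 3.34 govern re-registration, and canceled patients still owe on-study, flow-sheet and follow-up forms, so an as-randomized analysis is possible. Defining the analysis set is commonly left to a statistical analysis plan, and its absence here is not the fault. What remains is a rule that the protocol itself sets badly. A one-arm, post-randomization event is classed as eligibility, it is checked at re-registration, and power rests on a word that the protocol elsewhere uses as the opposite of ineligible.

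**Cancellation.** A reader might take 4.7 as a second 5-FU-only exit. It is not. It is optional, and it refers to assigned treatment generally. A control B3/C patient who never begins adjuvant therapy has had no protocol therapy and may be canceled, whereas a patient who began the infusion may not. That route can work against the direction claimed above. Its net direction is uncertain, and the rule differs by group.

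**Day 35, performance status and blood counts.** These might look like further filters on the 5-FU arm. They apply to both arms (3.22–3.23, 3.28, 3.32–3.33, 3.35), and an equivalent control fails them too. They are no part of the one-arm argument.

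**The inputs are assumed.** This also stands. Non-starting for logistic reasons is plausible, since 4.5 stresses completing randomization in time for the 24-hour limit. If that is the only cause, there is no bias at any share.

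**Conclusion.** The point holds in conditional form. Sections 3.13, 3.27 and 3.34 set a condition that one arm alone can fail after randomization. If it decides who is analyzed, the B3/C comparison can be biased, probably toward 5-FU when non-starters have a worse prognosis. If it decides only who is re-registered, the arms differ in access to protocol adjuvant therapy; that effect has not been sized.

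The error ranges from about 5% (equal hazard) through 6.4% and 9% to 15% (2%, 5% and 10% non-starters at twice the hazard). These figures assume no true effect, deletion of every non-starter from the 5-FU arm and of no control, and values of f and m that are not in the protocol. They show what is at risk and are not an estimate of what happened. The documents do not support saying that the comparison is biased as a matter of fact.

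**What to change.** 1. State in 9.0 that the primary comparison includes every randomized patient whose institutional pathology is Dukes' B3 or C, in the assigned arm, timed from randomization, regardless of 5-FU start, re-registration or cancellation. Replace the undefined term analyzable with this definition.
2. Take the 24-hour start out of 3.13, 3.27 and 3.34 and record it as a treatment-compliance item. The clinical instruction already stands in 5.21 and is not touched.
3. In 4.7, state that cancellation is an administrative status with no effect on the analysis in any group. Correct the reference in 4.24 to a Section 3.4 that does not exist.
4. Restate the power for a plausible non-starter share.

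**Cost.** Items 1 to 3 are wording, and the follow-up they need is already required of canceled patients. The real cost is dilution, which is more than slight at a 5% or 10% share. Either the lower power is accepted and stated, or accrual rises to about 2217 (5%) or 2470 (10%). Section 9.0 already foresees revising the accrual goal.
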